### 10.7. Analysis methods – exploratory and other outcomes

As indicated in the protocol there are a number of exploratory outcomes within the IIH:DT trial, the details of these analyses are documented separately, as they are not being undertaken within the Birmingham Clinical Trials Unit (BCTU).

### 10.8. Sensitivity analyses

Sensitivity analyses will be limited to the primary outcome and will consist of:

- Per-protocol analysis (population described in section 9.2);
- An analysis to assess the effect of missing responses using multiple imputation and last observation carried forward (the primary outcome is only collected at baseline and 12 weeks, so this is carrying forward the baseline ICP to 12 weeks, which is essentially assuming no change);
- An analysis to assess the effect of late assessments by including only those returned within the assessment window in the analysis.
- An analysis to assess the effect of any distributional assumptions (details provided in section 9.11);
- An analysis to assess the effect of any outliers.

### 10.9. Planned subgroup analyses

There are no planned subgroups analyses for this trial.

### 10.10. Safety data

No formal hypothesis testing of safety data is planned, although appropriate statistical techniques may be used to better understand the emerging safety profile if necessary.

The AE data will be summarised descriptively, as the number of AEs reported, and the number and percentage of patients reporting an AE by system organ class by treatment arm. The SAEs will also be summarised descriptively and tabulated as the number and percentage of patients experiencing an SAE by treatment arm. Information on relatedness to treatment will also be included for both AEs and SAEs.

Safety bloods are collected at: baseline; week 1; week 4; week 8; week 12; and week 16. Safety data on renal function (urea, creatinine, potassium, sodium), liver function (AST, ALT, ALP, bilirubin, albumin, γGT), thyroid function (TSH, fT4), muscle function (creatinine kinase) and HPA (cortisol, DHEA, androstenedione, testosterone, ACTH, FSH, LH, oestradiol, progesterone) will be reported. For each measure, the mean and 95% confidence interval at each point by treatment arm will be calculated. The proportion of patients who has values above the upper reference limit or above the trial upper limit (e.g. AST, ALT, bilirubin) will be calculated.

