## **2. Background and rationale**

The background and rationale for the trial are outlined in detail in the protocol. In brief, IIH:DT is a trial in participants who have idiopathic intracranial hypertension (IIH) which is characterised by elevated intracranial pressure (ICP) and papilloedema. IIH is a condition found almost exclusively in obese women (90%) and causes disabling daily headaches and loss of vision, which is severe and permanent in up to 25% of cases. It is hypothesised that 11 $\beta$ -HSD1 amplifies local cortisol availability at the choroid plexus, thereby increasing cerebrospinal fluid secretion which may increase ICP. Therefore use of an 11 $\beta$ -HSD1 inhibitor may lead to decreasing ICP in IIH.

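### The planned out-of-range proportions for the safety bloods count high values only; the SAP has no count below a lower reference limit

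*SAP*

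**What the plan says.** SAP section 10.10 names the safety bloods by organ system. They include "Safety data on renal function (urea, creatinine, potassium, sodium", then "liver function (AST, ALT, ALP, bilirubin, albumin" and γGT, two thyroid measures, a muscle enzyme, and "HPA (cortisol, DHEA, androstenedione, testosterone, ACTH, FSH, LH, oestradiol, progesterone) will be reported". Samples are taken at baseline and weeks 1, 4, 8, 12 and 16.

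Two summaries are fixed for these bloods:

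- A summary of the average level: "For each measure, the mean and 95% confidence interval at each point by treatment arm will be calculated".
- A count against limits, for which AST, ALT and bilirubin are given as examples: "The proportion of patients who has values above the upper reference limit or above the trial upper limit".

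The first describes the arm. The second is the only one that counts patients, and it looks upward only. No lower reference limit, lower trial limit, count outside range in either direction, or shift table appears in section 10.10 or elsewhere in the SAP. The version 2.0 entry in the change log describes the same upper-limit rule, adding that it applies where suitable.

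Two other provisions of section 10.10 bear on the point. On adverse events: "The AE data will be summarised descriptively, as the number of AEs reported", with patients counted by system organ class and arm. And there is a discretionary clause: "appropriate statistical techniques may be used to better understand the emerging safety profile if necessary".

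**The concern.** An upper limit suits measures such as AST, ALT and bilirubin. It does not suit all of the list. Low albumin is usually the finding of interest, and sodium, potassium, thyroid and HPA measures can be abnormal in either direction. A patient-level count that looks only upward leaves part of the listed safety data without a tabulation of its abnormal values.

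Safety and tolerability of the 12-week course is a stated secondary objective (SAP section 3). In a trial of 30 people, safety signals in blood results are likely to be a few individual values, and arm means show those poorly. If low values are left out, the comparison of abnormal results between arms covers one direction only.

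**Working it through.** **Inputs**

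- 15 participants per arm (SAP section 8).
- Mean and 95% CI per arm and visit, and the proportion above an upper limit (SAP section 10.10).
- Assumptions, because the SAP gives no reference ranges or SDs for the bloods: each analyte is scaled to its own SD, the other participants are centred on the reference mean, and (step 5) values are normal with a reference range of mean ± 1.96 SD.

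**1. The plan's own figure.** A 14% difference with SD 10% is a standardised difference of 14/10 = 1.4. The two-sample t-test at 90% power and two-sided 0.05 needs 11.77, so 12 per group. Allowing 20% dropout, 12/0.8 = 15. The SAP's 15 per arm is reproduced and is not in dispute.

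**2. What is on the list.** Renal 4, liver 6, thyroid 2, muscle 1, HPA and sex hormones 9: 22 measures. At least sodium, potassium, albumin, TSH, fT4, cortisol and ACTH can be read as having a meaningful low side. That is general clinical knowledge; the SAP states no directions of concern.

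**3. How far one or two low values move a mean.** A participant at −3 SD shifts an arm mean of 15 by 3/15 = 0.2 SD. Two shift it by 6/15 = 0.4 SD. The 95% CI half-width for SD 1 is t(0.975, 14 df)/√15 = 2.145/3.873 = 0.55 SD. Both shifts lie inside it. The low values also inflate the sample SD, which widens the interval further.

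**4. The same with the SD inflation included.** Take k of 15 at −2.5 SD and the rest with mean 0 and SD 1. Then mean m = −2.5k/15 and variance = [(15−k) + (15−k)m² + k(−2.5−m)²]/14.

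| Low values of 15 | Share below range | Arm mean (SD) | 95% CI | Added to upper-limit count |
|---|---|---|---|---|
| 1 | 6.7% | −0.17 | −0.83 to 0.49 | 0 |
| 2 | 13.3% | −0.33 | −1.06 to 0.39 | 0 |
| 3 | 20.0% | −0.50 | −1.27 to 0.27 | 0 |

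Check for k = 3: variance = (12 + 12×0.25 + 3×4)/14 = 27/14 = 1.93, SD 1.39, half-width 2.145×1.39/3.873 = 0.77. Even with three of 15 clearly low, the interval still covers the reference mean.

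**5. A shift of the whole arm.** With a downward shift of s SD, the share below the lower limit is Φ(−1.96 + s) and the share above the upper limit is 1 − Φ(1.96 + s).

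| Shift (SD) | Below lower limit | Expected of 15 | Above upper limit |
|---|---|---|---|
| 0 | 2.5% | 0.4 | 2.5% |
| 0.5 | 7.2% | 1.1 | 0.7% |
| 1.0 | 16.9% | 2.5 | 0.15% |
| 1.5 | 32.3% | 4.8 | 0.03% |

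A shift of 1 SD or more exceeds the 0.55 SD half-width and should show in the planned means. A 0.5 SD shift may not. In each case the planned proportion falls as low values become more common.

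**The case against.** The strongest reply is that the plan is not blind to low values and does not order a high-only flag for everything. Several stronger readings that a reader might infer are indeed not supported:

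- **That low values are never counted.** A low result reported as an adverse event enters the adverse event tables, and a general fall would show in the visit means. The gap is in the planned out-of-range proportions.
- **That the upper-limit rule applies to every analyte.** The each-measure wording belongs to the sentence on means. The proportion sentence gives only AST, ALT and bilirubin as examples, and the change log suggests selective use. The text does not say which analytes are flagged.
- **That the table would declare low results normal.** A zero would mean that none were above the upper limit. The output would be incomplete, not false.
- **That the drug's mechanism predicts low blood cortisol.** SAP section 2 offers a hypothesis that the enzyme "amplifies local cortisol availability at the choroid plexus". It does not say that serum cortisol falls.

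It can also be said that the upper-limit summary was a deliberate choice, recorded before database lock, that the safety analysis is descriptive, and that the protocol, not shown here, may set monitoring limits.

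All of this limits the claim without removing it. Selective flagging would leave the remaining analytes with no patient-level count in either direction. Adverse event tables capture a low value only if someone reports it. The discretionary clause commits to nothing, and the outlier and distribution checks in section 10.8 are confined to the primary outcome. Monitoring limits in a protocol would not alter a reporting rule that the SAP states itself.

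**Conclusion.** The point holds as a gap in descriptive safety reporting. The only planned patient-level summary of the safety bloods is upward, while the list contains measures for which a low value can be the signal. One or two participants of 15 at −3 SD would move an arm mean by 0.2 to 0.4 SD against a half-width of about 0.55 SD, and would add nothing to the planned proportion.

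The sizes rest on 15 evaluable participants per arm and on analytes scaled to their own SD; the range-based figures also assume normality. Which analytes have a meaningful low side is a clinical judgement that the SAP does not record, but albumin, sodium and potassium carry the point without any appeal to mechanism. The primary analysis, the sample size and the type I error are untouched. It should be corrected, but it does not threaten the trial's main conclusion.

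**What to change.** Amend section 10.10 to report also, by arm and visit, the number and percentage of participants below the lower reference limit for each analyte where low values matter. Keep the existing upper reference limits and trial upper limits. The clinical team should name, in the same paragraph, which analytes are counted on the low side, the high side or both, which also settles the present uncertainty about where the upper-limit flag applies.

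The cost is a short addition to the text and extra table columns. The bloods are already collected at all six time points and the plan already uses laboratory reference limits; the assumption is that the lower limits are available from the same source. No new data, testing or change to the sample size is needed.

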## 11. Output from sub-randomisations

Not applicable.

|                                     |
|-------------------------------------|
| 12. Health economic analyses |
|-------------------------------------|

|                                                        |
|--------------------------------------------------------|
| No health economic analysis is planned for this study. |
|--------------------------------------------------------|

|                                 |
|---------------------------------|
| 13. Statistical software |
|---------------------------------|

|                                                                                                          |
|----------------------------------------------------------------------------------------------------------|
| SAS software, version 9.4 (or higher) and/or Stata version 14 (or higher) will be used for all analyses. |
|----------------------------------------------------------------------------------------------------------|

|                       |
|-----------------------|
| 14. References |
|-----------------------|

- |                                                                                                                                                                                                                                                                                                                                                                                                                                                                                                                                                                                                                                                                                                                                                                                                                                                                                                    |

|----------------------------------------------------------------------------------------------------------------------------------------------------------------------------------------------------------------------------------------------------------------------------------------------------------------------------------------------------------------------------------------------------------------------------------------------------------------------------------------------------------------------------------------------------------------------------------------------------------------------------------------------------------------------------------------------------------------------------------------------------------------------------------------------------------------------------------------------------------------------------------------------------|

## Appendix A – Deviations from SAP

This report below follows the statistical analysis plan dated <insert effective date of latest SAP> apart from following:

| Section of report not following SAP | Reason                                             |
|-------------------------------------|----------------------------------------------------|
| <insert section >                   | <insert, e.g. exploratory analyses request by TMG> |

## Appendix B – Trial schema

[figure not shown]

## Appendix C – Schedule of assessments

|                                          |                                                                        | Screening |   |   |   |   |   |   |   |    |         |        |    |
|------------------------------------------|------------------------------------------------------------------------|-----------|---|---|---|---|---|---|---|----|---------|--------|----|
|                                          |                                                                        |           | 0 | 1 | 2 | 3 | 4 | 6 | 8 | 10 | 12 - D1 | 12- D2 | 16 |
| Primary outcome                   | Lumbar puncture & CSF sampling                                         | ■         |   |   |   |   |   |   |   |    | ■       |        |    |
| ICP                               |                                                                        |           |   |   |   |   |   |   |   |    |         |        |    |
| Secondary outcomes                | BMI, waist/hip ratio,                                                  | ■         |   |   |   |   |   |   |   |    | ■       |        | ■  |
| Weight                            | DXA scanning                                                           |           | ■ |   |   |   |   |   |   |    |         | ■      |    |
|                                          | Blood pressure                                                         | ■         |   |   |   |   |   |   |   |    | ■       |        |    |
| Visual assessments                | Visual acuity and contrast sensitivity                                 | ■         |   |   |   |   |   |   |   |    | ■       |        | ■  |
|                                          | Humphrey visual field mean deviation                                   | ■         |   |   |   |   |   |   |   |    | ■       |        | ■  |
|                                          | Optical coherence tomography                                           | ■         |   |   |   |   |   |   |   |    | ■       |        | ■  |
|                                          | Retinal photographs (Frisen grade and “Better, worse, same evaluation” | ■         |   |   |   |   |   |   |   |    | ■       |        | ■  |
|                                          |                                                                        |           |   |   |   |   |   |   |   |    |         |        |    |
| Headache                          | Headache impact test 6                                                 | ■         |   |   |   |   |   |   |   |    | ■       |        | ■  |
|                                          | Headache diary (frequency (days / weekly), severity & duration)        | ■         |   |   |   |   |   |   |   |    | ■       |        | ■  |
|                                          | Analgesic use (days/week)                                              | ■         |   |   |   |   |   |   |   |    | ■       |        | ■  |
| Metabolic evaluation              | 24 hours urine sampling                                                | ■         |   | ■ |   |   | ■ |   | ■ |    | ■       |        | ■  |
|                                          | Fat biopsy                                                             |           | ■ |   |   |   |   |   |   |    |         | ■      |    |
|                                          | Prednisolone generation curve                                          |           | ■ |   |   |   |   |   |   |    |         | ■      |    |
|                                          | DXA scanning                                                           |           | ■ |   |   |   |   |   |   |    |         | ■      |    |
| Medical assessment                | History, +/-examination, compliance                                    | ■         |   | ■ | ■ | ■ | ■ | ■ | ■ | ■  | ■       |        | ■  |
|                                          | Venesection                                                            |           | ■ | ■ |   |   | ■ |   | ■ |    |         | ■      | ■  |
|                                          | Pregnancy test                                                         | ■         |   | ■ |   |   | ■ |   | ■ |    | ■       |        | ■  |
| Serious adverse events monitoring |                                                                        |           |   | ■ | ■ | ■ | ■ | ■ | ■ | ■  | ■       |        | ■  |

## Appendix D – CONSORT flow diagram

[figure not shown]

Supplement: fcz050_Supplementary_Data [file fcz050_supplementary_data.zip › Statistical_analysis_plan.pdf]
